### Data management

Data Collection: All data collected during the study will be recorded electronically and stored on secure, encrypted servers. All study participants will be assigned a unique identifier to maintain confidentiality and to link data from different visits and assessments. Participant retention: All individuals participating in the study will be provided with a comprehensive report of the clinical assessments performed, which include physical and neurological examinations, MRI results, PSG clinical report, LP clinical results (cell count, protein and glucose levels), biomic blood tests, and cognitive assessments. In accordance with the participants’ preferences, the Principal Investigator (PI) will communicate all significant clinical data to their family physician, thereby promoting preventive medicine and the overall health of the participants. Additionally, annual webinars will be arranged to update the participants about the progress of the study and advancements in the related research field. Contact information for both the PI and the study coordinator will be made available to the participants, who will be encouraged to reach out to the study personnel with any questions or concerns.

Data Quality Control: To ensure data quality, a trained research assistant will perform regular data entry checks, and all data will be reviewed by the principal investigator to identify and resolve any discrepancies. Data monitoring: The local and the Ministry Of Health (MOH) IRB’s are responsible for conducting periodic audits on the conduct of the trial. The study meets all of the ethical and regulatory requirements for data collection and use and does not require additional oversight. Data Backup: Daily backups of all study data will be stored off-site, in a secure location, to ensure data integrity and protect against loss or corruption. Data Access: Only authorized personnel, who have completed confidentiality agreements, will have access to the study data. All study personnel will be trained on data security protocols. Data Analysis: Statistical analysis of the data will be performed using appropriate software. Data will be examined for normalcy and homogeneity based on scatter plots and histograms. Differences between groups on clinical and biological measures will be performed using General Linear Models for repeated measures. Estimation of risk based on aggregated measures will be done using cox regression. Data Sharing: The study data will be shared with relevant researchers and institutions in accordance with the study’s approved data-sharing plan. All data sharing will be done in a secure and confidential manner, and in compliance with relevant privacy regulations. Communication of trial results will be done via publication in scientific journals and professional conventions, or other data-sharing arrangements. Data Archiving: All study data will be archived and stored in a secure location for a minimum of 10 years after the completion of the study. Trial registration: The study is an observational study. It has registered retrospectively in https://clinicaltrials.gov/ and has been assigned an identification number NCT05746715.

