**Methods:**

The study has two groups: Patients diagnosed with gCJD, and first-degree healthy relatives (HR) (both carriers and non-carriers of the E200K mutation in the *PRNP* gene) of patients diagnosed with gCJD. At baseline, and at the end of every year, healthy participants are invited for an “in-depth” visit, which includes a clinical evaluation, blood and urine collection, gait assessment, brain MRI, lumbar puncture (LP), and Polysomnography (PSG). At 6 months from baseline, and then halfway through each year, participants are invited for a “brief” visit, which includes a clinical evaluation, short cognitive assessment, and blood and urine collection. gCJD patients will be invited for one “in-depth” visit, similar to the baseline visit of healthy relatives.

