## Background

Creutzfeldt-Jakob Disease (CJD) is the most common prion disease in humans. It results from a conformational change of the normal prion protein (PrP^c^) into a pathological protein (PrP^sc^) that aggregates in the central nervous system [1]. Once formed, the initial PrP^sc^ oligomers can act as seeds for further misfolding of normal cellular PrP^c^ in a cascade that leads to neuronal death, as well as to the clinical manifestations of the disease.

Early symptoms are nonspecific and may include headaches, anxiety, and behavioral changes. Later, diffuse neurological impairment appears, including cognitive decline, cerebellar ataxia, pyramidal, and extrapyramidal deficits, disturbances of vision, and myoclonus. CJD can be etiologically classified into transmitted, sporadic (sCJD), and genetic forms (gCJD). The familial forms are caused by mutations in the PRNP gene that encodes for the prion protein (PrP). The largest cluster of gCJD cases exists in Jews of Libyan and Tunisian ancestry, carrying an E200K mutation (Glu to Lys substitution) in the *PRNP* gene. Approximately 200,000 Libyan Jews live in Israel, resulting in the largest population of at-risk individuals in the world [2].

The disease is invariably fatal, and survival is between several months to 1 year [3], with a mean survival from onset to death of 7.6 months [4]. Thus, by the time the disease is diagnosed, the neural pathology is extensive, and the neurodegeneration is vast. The presence of a genetic mutation may help identify individuals at risk for developing the disease as the penetrance of the mutation approaches 100% [5]. Carriers of the E200K mutation are born with this dominantly inherited mutation, but most remain asymptomatic until middle age, and some develop the disease as late as 80 years old [5].

E200K-PrP is initially formed as a normal PrP^c^ isoform [6]. Therefore, the mutation is not necessarily sufficient for the formation and accumulation of PrP^sc (6)^. This fact suggests that other, genetic and non-genetic factors affect the age at symptoms onset. The *CYP4 × 1* gene may influence the age at onset in patients with gCJD due to the E200K mutation and in sCJD [7]. Inheritance of gCJD with E200K mutation may exhibit anticipation (an earlier symptom onset or more severe presentation in offspring) [8]. However, this claim requires further investigation [9]. Other modifiers remain obscure.

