### Sample size calculation and statistical analysis

With the objective of identifying biological markers for early detection of gCJD, we intend to conduct a comparative analysis of marker levels between gCJD patients and healthy individuals, as well as between healthy carriers and non-carriers. Based on the Israel National Registry for CJD, the annual incidence rate of CJD is 51 cases, although this is believed to be an underestimation. About two-thirds of the reported cases are familial cases, and of these cases, almost all are carriers of the E200K mutation. Given our conservative estimate that 50% of new cases of gCJD will be referred to our center, we anticipate that we will receive 15 new gCJD patients each year, for a total of 60 patients during the study period. Furthermore, we anticipate that approximately one-third of these patients, or 20 in total, will be willing to participate in the study.

With a conservative estimation of 3 first-degree HR per gCJD patient, this enables a population pool of > 100 per study period. As the E200K is an autosomal dominant mutation, 50% of the first-degree relatives of gCJD will carry the mutation. Based on Spudich et al. [34], the likelihood of developing gCJD is 0.45 in the age group of 51–60. According to Minikel et al., the average annual probability of onset (phenoconversion) for healthy carriers aged 40 to 80 years is 4.6% [35]. The primary aim of the study relates to biological markers for identifying phenoconversion. In our study, we referred to a positive CSF RT-QuIC.

CSF RT-QuIC has proven to be a relatively sensitive (73-97%) [13, 14] and a highly specific biomarker (99-100%) [12, 15–17] for diagnosing CJD, and it is now part of the standard diagnostic criteria [10]. Thus, considering a conservative estimate of a 13.6% phenoconversion rate among carriers (calculated as 3.4% expected conversion per year for 4 years) a sample size of 106 healthy relatives (53 carriers and 53 non-carriers) is required, based on a desired probability of type 1 error of 0.05 and a power of 80% (https://clincalc.com/stats/samplesize.aspx).

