Secondary outcomes relating to the risk of phenoconversion will be also examined. With the objective of identifying risk factors for phenoconversion, we intend to conduct a comparison between groups (gCJD patients vs. HR), and within the HR group (carriers vs. non-carriers). We also intend to perform a Cox proportional hazards analysis. The analysis is based on the concept of hazard, which is a measure of the instantaneous risk of the event occurring at a given time. The Cox model assumes that the hazard for each individual is proportional to the hazard for others over time, and can be represented as a combination of individual-specific factors and their coefficients. The coefficients from the Cox model can be used to estimate the relative risk of phenoconversion for each factor, with larger coefficients indicating a greater risk of disease onset. By examining the relationship between the risk factors and phenoconversion time, Cox proportional hazards analysis can help identify which factors are most important in determining the risk of disease onset, allowing for the development of predictive models and the identification of potential targets for intervention.

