The justification for the need for LP in this study is based on several factors. Firstly, CJD is a rapidly progressive disease, and early detection is critical for improving patient outcomes. The yearly analysis of the CSF may help identify prodromal changes in brain biomarkers, particularly the aggregation of PrP^sc^, which may indicate onset of disease before appearance of clinical symptoms. Secondly, the protocol has been granted approval by the ethics committee, taking into account the exceptionally high penetrance of the mutation and the valuable data that can only be obtained from CSF. This taken together with the fact that the LP procedure is considered safe led the committee to decide that its potential benefit outweighs the risk. Thirdly, participants who are not willing to repeat the LP procedure are not excluded from the study. However, in the event that they exhibit symptoms suggestive of conversion into the disease, an LP is carried out as part of the clinical diagnostic process. This ensures that participants are given the option to opt-out of the LP procedure while still receiving the necessary medical attention should they develop symptoms. In conclusion, there is a need for lumbar puncture in healthy carriers of the E200K mutation for CJD as part of a clinical trial studying the natural history of the disease and the prodromal phase. CSF sampling in a high risk healthy population is critical in order to identify markers associated with the prodromal phase of the disease and therefore was approved by the ethics committee. Participants who do not wish to undergo LP are not excluded and are able to participate in the study.

All gCJD patients will be scored according to the National Prion Monitoring Cohort (NPMC) Scale (MRC Prion Disease Rating Scale) [36], which is a multimodal scale assessing both cognitive impairment and daily function disability. This scale consists of 11 parameters: bowel function, bladder function, toilet use, bathing, feeding, transfer and mobility, stairs, best verbal response, memory and orientation to surroundings, judgment and problem-solving, and use of tools. Each section is scored between 0 and 4 with 0 indicating complete disability and 4 normal ability, for a maximum of 20 points.

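### The repeated-measures General Linear Model named for group differences does not fit patients seen once and, in its classical form, drops most converters from the marker trajectories

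*Protocol article*

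**What the plan says.** The Data Analysis text under Data management gives the method for comparing groups: "Differences between groups on clinical and biological measures will be performed using General Linear Models for repeated measures". It assigns estimation of risk to Cox regression. No other method for group differences on measures is named.

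The comparisons are set out under Sample size calculation and statistical analysis: "we intend to conduct a comparison between groups (gCJD patients vs. HR), and within the HR group (carriers vs. non-carriers"). The same section applies both contrasts to marker levels.

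The design those comparisons meet is as follows.

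- **Patients.** Abstract, Methods: "gCJD patients will be invited for one “in-depth” visit, similar to the baseline visit of healthy relatives". Study design adds that patients do only the assessments they are able to complete. The sample size section expects that "approximately one-third of these patients, or 20 in total, will be willing to participate in the study".
- **Relatives.** In-depth visits at baseline and at 12, 24, 36 and 48 months, with brief visits halfway through each year (Study design, Imaging, Discussion). An extra lumbar puncture and MRI are done when phenoconversion is suspected (Lumbar puncture, Imaging).
- **Incomplete CSF.** Clinical neurological and cognitive evaluation: "participants who are not willing to repeat the LP procedure are not excluded from the study".
- **Survival after onset.** Background gives a range of several months to one year, "with a mean survival from onset to death of 7.6 months".
- **Families.** Relatives are recruited through patients, "With a conservative estimation of 3 first-degree HR per gCJD patient".

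**The concern.** A repeated-measures model compares groups on a series of values within each person. One of the two planned contrasts has a group with no series at all, so the method and the comparison do not match.

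For relatives the difficulty is what happens to incomplete series. The procedure usually meant by this name holds one row per person with a fixed column per visit, and drops any row with a gap. A relative who converts early in follow-up is unlikely to be alive at month 48, so the row has a gap. Measurements taken when conversion is suspected fall off schedule and have no column. A relative who gives CSF at baseline and then declines a repeat would lose the baseline value as well.

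The stated aim is to find markers of preclinical disease. If the marker trajectories come mainly from people who stayed well and attended every visit, they are pulled towards no change, and the people whose earlier samples matter most are left out.

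**Working it through.** **1. The plan's own figure.** The sample size section gives 106 relatives (53 carriers, 53 non-carriers) for 13.6% conversion, alpha 0.05 and power 80%. Taking 0% in non-carriers (assumed, since it is not stated) and a two-sided test with no continuity correction:

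n per group = [1.96 × √(2 × 0.068 × 0.932) + 0.8416 × √(0.136 × 0.864)]² / 0.136² = 52.6, rounded up to 53.

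Total 106; power at 53 per group is 80.3%. The figure reproduces and is not in dispute. It sizes a binary endpoint, not the repeated-measures analysis.

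**2. Patients against relatives.** Expected patients: 20. Visits each: 1. Patients with a repeated series: 0 of 20.

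**3. Converters.** Expected number: 53 × 0.136 = 7.2. Assume conversion is uniform over 48 months and everyone survives the same time S after onset. The share still alive at month 48 is S/48.

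| S | Alive at month 48 | Series cut by death | Of 7.2 converters |
|---|---|---|---|
| 7.6 months (mean in Background) | 7.6/48 = 16% | 84% | 6.1 |
| 12 months (upper end in Background) | 12/48 = 25% | 75% | 5.4 |

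This counts death alone, before any inability to complete lumbar puncture, MRI or sleep recording.

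**4. Other relatives.** The article gives no attendance figure, so this is illustration. With independent attendance of 95%, 90% or 80% at each in-depth visit, the share with all five is 0.95⁵ = 77%, 0.90⁵ = 59% or 0.80⁵ = 33%.

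**5. Family.** The intraclass correlation (ICC) is not given, so 0.1, 0.3 and 0.5 were tried. Single-time-point t-tests that ignore family were simulated with 35 families of three (4,000 replicates, nominal error 0.05).

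| ICC | Type I error, carrier status | Type I error, factor shared by the whole family |
|---|---|---|
| 0.1 | 0.047 | 0.072 |
| 0.3 | 0.045 | 0.112 |
| 0.5 | 0.050 | 0.165 |

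Carrier status varies within families, and ignoring family does little harm to that contrast at one time point.

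**The case against.** The article never says that incomplete series are deleted. It names a model class and leaves the software open, and missing-data rules are commonly left to an analysis plan. It calls the study both cross-sectional and longitudinal and likens the patient visit to the relatives' baseline visit, so a baseline comparison may well be intended. An ordinary linear model would fit that.

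Much of this stands. The patient contrast can be made with the data to be collected; what does not fit is the method named for it. The deletion of incomplete series follows from the classical form of the method, not from a written rule. But the article does commit itself to a method, and in its usual sense that method conflicts with the design described, so this is more than detail left out.

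Stronger readings that a reader might infer do not hold:

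- **Converters are lost from the study.** They are not. Cox regression handles risk of conversion and uses incomplete follow-up.
- **Nearly all converters drop out of the trajectories.** The supported statement is most, about 75-84% of some 7 people, under assumed timing.
- **Clustering shrinks the 106 relatives to a much smaller effective number.** A design effect of 1 + (3 − 1) × ICC concerns factors shared by a whole family. Neither planned contrast is of that kind, and the carrier contrast kept its error near 0.05. Three is also the size of the recruitment pool per patient, not of enrolled families.
- **Everyone who refuses lumbar puncture loses CSF data through the method.** Those who never have one have no routine CSF under any model. Only those who decline a repeat are affected.
- **The patient contrast is confounded by age.** Entry ages differ (18 or older against 50 or older), but the actual age gap is unknown, and covariates and transformations are commonly left to the analysis plan.

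**Conclusion.** The concern holds in limited form. The only method named for group differences does not fit the patient against relative comparison, because 0 of 20 expected patients have repeated measures. That part rests on the article alone.

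In its classical form the method would also remove from the CSF analyses relatives who decline a repeat lumbar puncture, and from the marker trajectories about 5.4 to 6.1 of 7.2 expected converters. That part rests on three assumptions: listwise deletion, conversion uniform over 48 months, and a fixed survival of 7.6 to 12 months. The damage is to marker trajectories; the Cox analysis and the sample size of 106 are untouched. Because those trajectories serve the study's main aim, the wording should be settled before analysis.

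**What to change.** Replace the single sentence with two.

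1. **Patients against relatives:** compare at one visit, the relatives' baseline against the patients' only visit, with an ordinary linear model.
2. **Carriers against non-carriers over time:** use linear mixed models on all available visits, including those triggered by suspected phenoconversion, with a participant random effect and fixed effects for group, time and their interaction.

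A family random effect is a sensible, cheap addition because relatives come in through patients, though it will change the carrier contrast little.

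The cost is a sentence or two and standard software, with no new data. The drawback is that a mixed model assumes data are missing at random given what was observed, and death after conversion may break that. A sensitivity analysis for the missing visits of converters is advisable; with about 7 converters it will have to be simple.

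### With about 20 patients and 106 relatives, an ordinary General Linear Model misstates the precision of the patients v relatives contrast if patients vary more, and the planned homogeneity check leads to no stated action

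*Protocol article*

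**What the plan says.** The analysis method is in the Data Analysis part of the Data management section: "Differences between groups on clinical and biological measures will be performed using General Linear Models for repeated measures". The sentence before it gives the assumption check: "Data will be examined for normalcy and homogeneity based on scatter plots and histograms". No residual variance structure is named, and no action is tied to the check.

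The group sizes are in Sample size calculation and statistical analysis. For patients, the article expects that "approximately one-third of these patients, or 20 in total, will be willing to participate in the study". For relatives, "a sample size of 106 healthy relatives (53 carriers and 53 non-carriers) is required". The same section plans two marker comparisons, and its paragraph on risk factors describes a "comparison between groups (gCJD patients vs. HR), and within the HR group (carriers vs. non-carriers"). Patients attend one in-depth visit (Abstract, Methods), so the patient contrast rests on a single time point.

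**The concern.** A General Linear Model in its usual form estimates one residual variance from all subjects. Here the relatives supply most of that estimate, while the uncertainty of the patient mean depends on the spread among only 20 patients. If patients vary more, the pooled variance is too small for them and the patients v relatives standard error is understated.

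Greater spread among patients is plausible from the article. The disease progresses rapidly, the entry criteria set no limit on stage, and the age floor is 18 for patients against 50 for relatives. Relatives are free of clinical CJD at entry. Plausible is not measured, however, and the ratio may differ from marker to marker.

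The article intends to identify markers partly by this comparison, and it lists 11 CSF and 5 blood markers besides MRI, sleep and gait measures. Understated standard errors could bring forward measures that do not differ, and would make the intervals for real differences too narrow.

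**Working it through.** **The plan's own figure.** The article states an error rate and power only for the 106 relatives: "based on a desired probability of type 1 error of 0.05 and a power of 80"%, with a "13.6% phenoconversion rate among carriers (calculated as 3.4% expected conversion per year for 4 years"). Taking 0% in non-carriers (implied, not stated), a two-sided test and mean proportion 0.068:

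n per group = [1.96 × √(2 × 0.068 × 0.932) + 0.842 × √(0.136 × 0.864)]² / 0.136² = (0.698 + 0.289)² / 0.0185 ≈ 53, so 106 in all.

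This reproduces, but it concerns a binary outcome. No error rate or power is stated for the General Linear Model contrasts.

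**Inputs for the patient contrast.** Patients 20 and relatives 106 (from the article); two-sided 5% level (sidedness assumed); relative SD 1 and patient SD r (r assumed, since the article gives no SDs); one value per person; normal data.

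**Formulas.**
- Pooled variance: (19r² + 105) / 124
- SE the model reports: √[pooled variance × (1/20 + 1/106)]
- True SE: √(r²/20 + 1/106)
- Type I error ≈ 2 × [1 − Φ(1.96 × reported SE / true SE)]; coverage of the 95% interval is 1 minus this

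**Example, r = 2.** Pooled variance = (76 + 105)/124 = 1.460. Reported SE = √(1.460 × 0.05943) = 0.295. True SE = √(0.2 + 0.00943) = 0.458. Ratio 0.64, and 2 × [1 − Φ(1.26)] ≈ 21%.

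| Patient/relative SD ratio | Reported/true SE | Type I error | Coverage of 95% interval |
|---|---|---|---|
| 0.75 | 1.22 | about 2% | about 98% |
| 1 | 1.00 | 5% | 95% |
| 1.25 | 0.86 | 9% | 91% |
| 1.5 | 0.76 | 13% | 87% |
| 2 | 0.64 | 21% | 79% |
| 3 | 0.54 | 29% | 71% |

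A simulation with groups of 20, 53 and 53 and one pooled residual variance (400,000 runs) gave 1.8%, 5.0%, 9.3%, 13.4%, 20.6% and 29.3%. The Welch test stayed at 5.0 to 5.1% over ratios 0.5 to 3.

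**Sensitivity to the number of relatives.** With 60 relatives (20 patients × 3 each), the error at ratios 1.5, 2 and 3 is about 11%, 15% and 20%.

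**Carriers v non-carriers.** Take a difference of 0.549 SD, which has 80% power with 53 per group.
- Fitted in relatives only, power stays at 80% and type I error at 5%, whatever the patient SD.
- Fitted in one model with the patients, the residual variance is (19r² + 104)/123. This inflates the SE by 1.09, 1.21 and 1.50 at ratios 1.5, 2 and 3. Simulated power falls to about 75%, 67% and 46%.

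**The case against.** The strongest reply is that a journal article condenses the plan. Variance structure, transformations and the response to a failed check often sit in an analysis plan, which is not shown here. The article does not say that variances are pooled, and it does plan to look at homogeneity. This limits the point: a remedy may exist elsewhere, and nothing says the investigators would ignore unequal spread. It does not remove the point. The article names a model whose usual form assumes equal variances, for groups of very unequal size. A look at plots corrects no standard error, and choosing a method after that look would be an unplanned, data-driven step.

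A reader might infer that both marker contrasts are wrong, with carriers v non-carriers losing power. The documents do not support that. The article places this contrast within the relatives, and nowhere says that patients share its model. Fitted in relatives only, it loses nothing.

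A reader might also take 13 to 29% as the error rate of this study. It is the result for SD ratios of 1.5 to 3, which are assumptions. At equal SDs there is no inflation, and if patients vary less the test is conservative.

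Lastly, a type I error requires equal means. The Background cites raised neurofilaments and tau in the serum of CJD patients, so false positives are not the realistic worry for those markers. This objection stands; what remains for them is intervals that are too narrow. The 106 relatives are also untouched, because that number rests on a binary RT-QuIC outcome.

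**Conclusion.** The point holds for patients v relatives and is conditional on patients varying more than relatives. The harm is false positives for measures that do not truly differ, and under-coverage for markers known to differ. The size rests on 20 against 106 subjects, one value per person, an ordinary pooled-variance fit and the assumed SD ratio; fewer relatives would soften it. For carriers v non-carriers there is no defect on the article's wording, only something to confirm. The change should be made, since it is cheap and the contrast is one of the two planned for finding markers.

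**What to change.** In the Data Analysis text, after the sentence naming General Linear Models, state that:
- every patients v relatives contrast uses group-specific residual variances (Welch, generalised least squares with variance by group, or HC3 standard errors), whatever the plots show;
- skewed fluid markers are analysed on the log scale;
- carriers v non-carriers is fitted in the relatives only.

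If the analysis plan already says this, a reference to it is enough.

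The cost is a sentence or two and a standard software option. Where patients do vary more, the patient-contrast intervals widen by about 1/0.76 = 1.3, 1/0.64 = 1.6 and 1/0.54 = 1.9 times at SD ratios 1.5, 2 and 3. That is a visible loss of apparent precision, but it is the correct width.
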